### Intolerance and over-dosage

The ability of individual infants to tolerate different PN components varies greatly, with age, gestation and clinical condition all contributing. This unpredictability requires regular and frequent biochemical monitoring described in LWH NICU PN guidelines. Clinicians and pharmacists will monitor PN tolerance and make necessary adjustments to PN administration as determined by daily clinical information and biochemical monitoring.

### Assessment of compliance with study PN

The amount prescribed is not necessarily the amount that a baby receives. Effectiveness of PN delivery is a secondary outcome for this study. Detailed and comprehensive information about the amount of PN infused is collected in the medical record. This will be transcribed to the CRF. This will allow accurate calculation of actual daily PN administration to individual patients. The results of these calculations will be recorded on the CRF. Expected daily PN is also recorded in the medical record. This will allow identification of any major deviation (>15 ml/kg/day) from the LWH guidelines. Non-trial PN will be administered until the infant is randomised. Following randomisation, administration of the non-trial PN/fluids may occasionally occur (eg severe hypoglycaemia, transfer to operating theatre or another centre). Administration of non-trial PN/fluids will still be fully recorded to allow full nutritional for the first 28 days to be calculated.

### Concomitant medications/treatments

These will be administered to all patients in accordance with the existing LWH PN guidelines and LWH NICU drug formulary. The study will not affect the use of concomitant medications/treatments.

## Methods: Assessments and Procedures

### Study schedule

The study schedule is summarised in Table 2. Randomisation will occur within 120 hours of birth. Following randomisation, baseline growth measurements will be performed. The study PN will be introduced at the earliest opportunity following randomisation. The process of collecting large amounts of routine monitoring data has been evaluated and refined in a previous study [51]

**Table 2 T2:** Daily flow chart summarising PN administration (maximum possible) and data collection

	PN administration (macronutrient content)								Week	Data collection (nutrition)					
**Age (d)**	**Protein (g)**		**Lipid (g)**		**Dextrose; PN (%)**		**Dextrose; Suppl (%)**		**1**	**Enteral/IV fluid intake (ICR)**	**U/EBG**	**Bone/LFT**	**TG**	**AA**	**Growth**
							
	**std**	**max**	**std**	**max**	**std**	**max**	**std**	**max**	**PN type**						

**1**	1.8	1.8	1.0	1.0	10	10	10	10	PN	•	•				•

**2**	1.8	1.8	1.0	1.0	10	10	10	10	Consent &	•	•	•			

**3**	2.4	2.9	1.9	1.9	10	12	10	12	randomise	•	•				•

**4**	2.4	2.9	1.9	1.9	10	12	10	12		•	•	•			

**5**	2.8	3.8	2.8	2.8	10	12	10	12		•	•				

**6**	2.8	3.8	2.8	2.8	10	12	10	12	SCAMP	•	•	•			

**7**	2.8	3.8	2.8	3.8	10	12	10	12	SCAMP	•	•		•	•	

	**PN administration (macronutrient content)**								**Week**	**Data collection (nutrition)**					

**Age (d)**	Protein (g)		Lipid (g)		Dextrose; PN (%)		Dextrose; Suppl (%)		**2-4**	Enteral/IV fluid intake (ICR)	U/EBG	Bone/LFT	TG	AA	Growth
							
	std	max	std	max	std	max	std	max	PN type						

**8**	2.8	3.8	2.8	3.8	10	12	10	12	SCAMP	•	•				•

**9**	2.8	3.8	2.8	3.8	10	12	10	12	SCAMP	•	•	•			

**10**	2.8	3.8	2.8	3.8	10	12	10	12	SCAMP	•	•				

**11**	2.8	3.8	2.8	3.8	10	12	10	12	SCAMP	•	•	•			

**12**	2.8	3.8	2.8	3.8	10	12	10	12	SCAMP	•	•				

**13**	2.8	3.8	2.8	3.8	10	12	10	12	SCAMP	•	•	•			

**14**	2.8	3.8	2.8	3.8	10	12	10	12	SCAMP	•	•		•	•	

Legend: Daily flow chart summary of SCAMP nutrition study protocol including consent, randomisation, PN administration and data collection. Week 2 flow chart is repeated in week 3 and 4 to complete the 28 day intervention period. Day 29: Patient reverts to standard PN (if still on PN). All routine data collection stops apart from routine weekly growth data which continues until 36 weeks corrected for gestational age.

Abbreviations: stnd: standard PN (scNPN); max: scNPN_max_; ICR: intensive care record of daily fluid/nutrient/drug administration; U/E, BG: routine biochemical monitoring of plasma electrolytes, glucose, lactate and blood gases; Bone/LFT: routine biochemical monitoring of plasma bone and liver biochemistry; TG: triglyceride levels; AA amino acid levels.

### Intravenous/enteral nutrition, fluid and drug infusion data

The hourly volume of each component of the intravenous/enteral nutrition, fluid and drug infusions is captured on routine nursing charts. Each 24 hour period will start at the time of birth and data will be collected for 28 completed days after birth.

### Biochemical/nutritional monitoring

Biochemical and nutritional monitoring will follow the protocol outlined in the LWH NICU PN guidelines (incorporated in the study schedule summary in Appendix 1).

### Growth monitoring

Occipitofrontal head circumference, weight, mid-upper arm circumference and lower leg length will be measured after 7, 14, 21, 28 days and then weekly until 36 weeks CGA.

### Infection monitoring

Monitoring for infection will follow the protocol outlined in the LWH NICU guidelines for infection. Daily CRP, white cell count (and neutrophils) and platelet data will be recorded in medical record and transcribed to the appropriate CRF for 35 days from birth.

### Line complications

Vascular access device usage and location data will be recorded including extravasation episodes resulting in skin/tissue injury.

### Neurodevelopmental follow-up

Following discharge, infants of this gestation have routine, out-patient, neurodevelopmental follow-up. Parents of study infants will be approached again at 2 years CGA, to request a formal neurodevelopmental assessment (Bayley III). This will replace one of the routine OP assessments and take place in the home (where possible). It will be performed by a consultant in paediatric neurodisability.

### Blood sampling and processing

PN blood tests: Routine biochemical monitoring will take place in accordance with LWH PN guidelines (Appendix 1, section 2.1.4). All blood samples will be processed according to standard practice and sent to the laboratories at the Royal Liverpool Children's Hospital (Alder Hey).

## Methods: Statistical Analysis

The primary outcome of the study will be assessed by comparing the groups allocated to scNPN and scNPN_max_.

### Sample size

A sample size of 75 (assuming a survival rate of 80% of recruited infants) in each group will have 80% power to detect a difference between the means of the 2 scNPN groups for the outcome head growth velocity over the first 28 days after birth of 6 mm. This assumes that the common standard deviation (SD) is 12 mm and analysis is based on using a two group t-test with a 0.05 two-sided significance level. The value for the SD is based on data gathered during a randomised controlled trial of nutrition on this unit [17] and previous audit ([name] unpublished data). This indicated that head growth velocity in the first 28 days was 24 mm/28d (SD12 mm). To maintain "normal" head growth (following the birth centile) a growth velocity of approximately 36 mm/28d is required at 24-28 weeks gestation. Head growth between birth and 28 days is has an approximately linear growth model (based on normal growth in utero). Thus the power calculation assumes that scNPN will achieve a mean growth velocity of 24 mm/28d (based on results from a nutritionally equivalent PN) and that the study has the power to detect an improvement in head growth to a mean growth velocity of ≥30 mm/28days using scNPN_max _assuming a common standard deviation of 12 mm.

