**Methods:**

We propose a single centre, randomised controlled exploratory trial of two standardised, concentrated neonatal parenteral nutrition regimens comparing a standard macronutrient content (maximum protein 2.8 g/kg/day; lipid 2.8 g/kg/day, dextrose 10%) with a higher macronutrient content (maximum protein 3.8 g/kg/day; lipid 3.8 g/kg/day, dextrose 12%) over the first 28 days of life. 150 infants 24-28 completed weeks gestation and birthweight <1200 g will be recruited. The primary outcome will be head growth velocity in the first 28 days of life. Secondary outcomes will include a) auxological data between birth and 36 weeks corrected gestational age b) actual macronutrient intake in first 28 days c) biomarkers of biochemical and metabolic tolerance d) infection biomarkers and other intravascular line complications e) incidence of major complications of prematurity including mortality f) neurodevelopmental outcome at 2 years corrected gestational age

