### Primary analysis

Primary analysis of the data will be by intention to treat, and will be done for all survivors. In order to test the hypothesis that the change in head circumference differs between the two groups while taking account of the clustering arising from multiple pregnancies, the primary outcome will be assessed using a general linear model.

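### Minor, wrong as written: 75 recruited per group at 80% survival gives about 77.5% power for 6 mm, not the stated 80%

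*Protocol article*

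**What the plan says.** The Sample size section of the protocol article states: "A sample size of 75 (assuming a survival rate of 80% of recruited infants) in each group will have 80% power to detect" a difference in "head growth velocity over the first 28 days after birth of 6 mm". It takes a common SD of 12 mm and expected means of 24 and 30 mm per 28 days. It also says that "analysis is based on using a two group t-test with a 0.05 two-sided significance level".

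Two other places fix how the 75 is to be read. The Methods part of the Abstract says "150 infants 24-28 completed weeks gestation and birthweight <1200 g will be recruited", so 75 per group is the number before deaths. The Primary analysis section says that the intention-to-treat analysis "will be done for all survivors", so infants who die do not contribute to the primary comparison.

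**The concern.** The sentence reports recruitment, expected survival and power together, so the allowance for deaths should already be inside the 75. Taking 80% of 75 leaves 60 analysed infants per group. For a standardised difference of 6/12 = 0.5, the usual requirement for 80% power is a little above 60 per group, so the three figures looked as if they could not all be right.

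This is the only power statement the article gives, and it concerns the primary outcome. If it is off, the stated type II error of 20% is too low, here by 2.5 points. A reader of a null result would then credit the trial with slightly more sensitivity than it was planned to have.

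**Working it through.** **Inputs, all from the protocol article**

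- Difference δ = 6 mm, SD σ = 12 mm, two-group t-test, two-sided α = 0.05, stated power 80% (Sample size).
- 75 per group with 80% survival of recruited infants (Sample size); 150 recruited in total (Abstract, Methods).
- Analysis in survivors (Primary analysis).

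**Step 1. Number analysed.** 75 × 0.80 = 60 per group, if the 80% is read as survival to the day 27-29 measurement.

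**Step 2. Attempt to reproduce the stated 80%.** For n per group, the test statistic has 2n − 2 degrees of freedom and noncentrality (δ/σ) × √(n/2). With n = 60 this is 0.5 × √30 = 2.739 on 118 degrees of freedom. Power is the probability that the noncentral t exceeds the two-sided 5% critical value in absolute size.

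| Analysed per group | Power, t-test | Power, normal approximation |
|---|---|---|
| 60 | 77.5% | 78.2% |
| 63 | 79.5% | 80.1% |
| 64 | 80.1% | 80.7% |
| 75 | 86.0% | 86.5% |

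The stated 80% is not reproduced at 60. Letting the number of survivors vary at random (binomial, 75 per group, 80%) gives an average power of 77.4%, so using the expected number is not the cause.

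**Step 3. Other readings.**

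- If 75 were the number analysed, power would be 86.0%, and the Abstract's 150 recruited would be contradicted.
- A one-sided 0.05 test at 60 per group also gives 86.0%, and the document specifies two-sided.
- The normal approximation at 60 comes closest, at 78.2%, but is still short, and the document names a t-test.

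**Step 4. What 80% would require.**

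- t-test: 64 analysed per group; 64 / 0.80 = 80 recruited per group, 160 in total.
- Normal approximation: n = 2 × (1.96 + 0.8416)² × (12/6)² = 62.8, so 63 analysed; 63 / 0.80 = 78.75, so 79 recruited per group, 158 in total.
- With 75 recruited, survival would have to be 64/75 = 85.3%.

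**Step 5. What 60 per group does support.** Solving the t-test power equation for 80% at n = 60 gives a detectable difference of 6.19 mm with SD 12 mm, or an SD of 11.63 mm with a 6 mm difference.

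**Step 6. Further losses (assumptions, not figures from the plan).** If another 5% or 10% of survivors had no usable measurement, 57 or 54 per group would be analysed and power would be about 75% or 73%. The document gives no such rates.

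**The case against.** The strongest reply is that the gap is within the rounding of the inputs. The SD and the difference are given to whole millimetres; an SD of 11.63 mm rounds to 12 and a difference of 6.19 mm rounds to 6. The article calls the trial exploratory, and no patient number or analysis would change. This stands as an argument about importance, and it is why the point is minor. It does not make the sentence right: on the inputs as printed, the recruitment figure is 4 or 5 infants per group short under either formula.

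A second reply is that the survival horizon is not stated. The matching 20% death figure in Table 3 sits among events recorded before 36 weeks, whereas the primary measurement is taken at 27-29 days, and a later death need not remove it. Infants unlikely to survive the first week are excluded, and parents are usually approached at about 48 hours, once the baby is stable. Survival to the measurement could therefore exceed 80%. This stands as a condition on the 77.5%. It does not rescue the claim, because about 85% would be needed, the document gives no day-28 survival, and 80% is the figure it uses in this calculation.

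A third reply is that the general linear model could recover the power. The Primary analysis section introduces that model to handle clustering from multiple pregnancies and names no covariates, and the power statement rests on a t-test. Any gain from adjustment would have no support in the document.

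**Conclusion.** The power statement is wrong as written, by a small amount: 77.5% instead of 80% under the named t-test, or 78.2% under the normal approximation. None of the readings tested gives 80%. The result rests on 80% surviving to the day 27-29 measurement, on every survivor being measured, and on treating infants as independent, as the plan's own t-test calculation does.

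A reader might go further in two ways that the document does not support. One is to conclude that the trial is seriously underpowered: a shortfall of 2.5 points does not show that, and the lower figures for 57 or 54 analysed depend on loss rates that the document does not give. The other is to attribute the 75 to multiplying an uninflated number by 1.2 instead of dividing by 0.8. The figures come close, but no inflation step is shown, so this is conjecture and the finding does not need it.

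**What to change.** Keep 150 infants and restate the one sentence in the Sample size section along these lines: 75 infants per group recruited, 60 per group analysed at 80% survival to the day-28 measurement, gives about 77.5% power to detect 6 mm (80% power for about 6.2 mm), with SD 12 mm and a two-sided 0.05 two-group t-test.

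If the sponsor quotes power after further losses, such as 57 or 54 analysed per group, those loss rates should be labelled as assumptions.

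The cost is one sentence and a slightly less favourable power figure. No extra infants are needed, and neither the conduct of the trial nor its analysis changes.

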### Analysis

A data analysis plan will be finalised when two thirds of participants have been recruited in order to allow the details of handling missing data to be based on experience with data collection. All analysis will be performed after data cleaning has been complete.

### Primary analysis

Primary analysis of the data will be by intention to treat, and will be done for all survivors. In order to test the hypothesis that the change in head circumference differs between the two groups while taking account of the clustering arising from multiple pregnancies, the primary outcome will be assessed using a general linear model.

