#### Primary objective

To compare the two allocation groups with respect to the rate of head growth from measurement made at enrolment to a measurement made between 27 and 29 completed days after birth (i.e. change in head circumference/(time of last measurement-time of first measurement)

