### Randomisation

Where feasible, randomisation should occur before 72 hours of age where possible but must occur within 120 hours. Randomization codes will be computer generated using the statistical package STATA. Once generated the randomisation lists will be sealed in opaque serially numbered envelopes and given to pharmacy to store in a secure place. The randomisation list will be stratified by gestation at birth: 24-26 and 27-28 completed weeks gestation at birth. Once a patient is consented in to the trial, pharmacy will open the next sequential envelope in the correct strata and provide the allocated interventions. Allocation concealment will be maintained except in the Pharmacy Department at Liverpool Women's Hospital. In the case of multiple births, each infant will be individually randomised.

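### The primary outcome starts at enrolment in the objective but covers the first 28 days of life in the abstract, hypothesis and sample size, and the power is not stated for the enrolment window

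*Protocol article*

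**What the plan says.** The Primary objective section gives the only full definition. The groups are compared on "the rate of head growth from measurement made at enrolment to a measurement made between 27 and 29 completed days after birth", with the formula "change in head circumference/(time of last measurement-time of first measurement" (bracket closed in the source). Study schedule agrees with this, since it places baseline growth measurements after randomisation. Randomisation aims for before 72 hours where possible but "must occur within 120 hours".

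Other sections use a different window:

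- Abstract, Methods: "The primary outcome will be head growth velocity in the first 28 days of life".
- Hypothesis: head growth velocity over the first 28 days of life.
- Sample size: the difference is specified "for the outcome head growth velocity over the first 28 days after birth of 6 mm", assuming that "the common standard deviation (SD) is 12 mm". The supporting data are reported for the same window: "head growth velocity in the first 28 days was 24 mm/28d (SD12 mm" (bracket closed in the source).

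Primary analysis words the hypothesis without any division by time: "In order to test the hypothesis that the change in head circumference differs between the two groups". The same sentence goes on to say that the primary outcome will be assessed with a general linear model.

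Two further facts bear on this. The Administration section says that every infant receives scNPN from birth until randomised. Table 2 marks a growth measurement on both day 1 and day 3, so a birth baseline and a near-enrolment baseline could both be on file.

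**The concern.** An analyst who has both a day 1 and an enrolment measurement finds support in the protocol for using either as the start of the primary outcome. The choice matters. Growth from birth includes up to about five days in which both arms receive the same nutrition, so a treatment effect that begins at randomisation is diluted. Growth from enrolment does not have this problem, but it is measured over a shorter interval, and the protocol gives no standard deviation for that interval.

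The estimate, its standard error and the power therefore depend on which section is followed. The Analysis section says the data analysis plan will be finalised only when two thirds of participants have been recruited. Until then the protocol is the main record of what the primary outcome is, and it should give one answer.

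**Working it through.** **Inputs (Sample size section unless stated).** Difference 6 mm (24 versus 30 mm/28 d); SD 12 mm; two-group t-test, two-sided 0.05; 75 per group with 80% survival, so 75 × 0.8 = 60 analysed per group. Randomisation up to 120 h (Randomisation); last measurement at day 27-29 (Primary objective).

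**Formula.** Noncentrality = difference / (SD × √(2/n)), with n per group and 2n − 2 degrees of freedom.

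**1. The plan's own figure.** 6 / (12 × √(2/60)) = 2.739. Power is 77.5% by the t-test (118 df) and 78.2% by the normal approximation. The stated 80% is reproduced only approximately. The t-test needs 64 analysed per group for 80%.

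**2. Outcome measured from birth, effect starting at randomisation.** Assume the 6 mm/28 d velocity difference applies only from day 3 or day 5, with the last measurement on day 28.

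- Start at day 3: 6 × 25/28 = 5.36 mm; t-test power 67.9%.
- Start at day 5: 6 × 23/28 = 4.93 mm; t-test power 60.7%.

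Both use SD 12 mm and 60 per group.

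**3. Outcome measured from enrolment.** Assume baseline at day 3 to 5 and last measurement at day 27 to 29. The window is then 27 − 5 = 22 days to 29 − 3 = 26 days. The same rate difference gives a change of 6 × 22/28 = 4.71 mm to 6 × 26/28 = 5.57 mm. Power then depends on how the SD behaves over the shorter window:

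| Assumption about the SD | SD of change, 22 to 26 days | t-test power, 60 per group |
|---|---|---|
| SD of the rate stays 12 mm/28 d | 9.43 to 11.14 mm | 77.5% |
| SD of the change scales with √time | 10.64 to 11.56 mm | 67.3% to 74.5% |
| SD of the change stays 12 mm | 12 mm | 56.9% to 71.3% |

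The documents neither give nor exclude any of these.

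**4. Rate versus raw change.** Assume window lengths uniform over 22-26 days. Their SD is 4/√12 = 1.15 days. At the average velocity of 27 mm/28 d this adds 1.15 × 27/28 = 1.11 mm, and √(12² + 1.11²) = 12.05 mm. With a wider spread of 22-29 days, the SD of the window is 7/√12 = 2.02 days, the added SD is 1.95 mm and the total is 12.16 mm. Power by the normal approximation then moves from 78.2% to about 77.1%. The scale of the outcome barely matters for the group comparison; the start point does.

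**The case against.** The strongest reply is that the Primary objective is a complete definition, the Study schedule supports it, and the abstract and hypothesis are shorthand. Under the approximately linear growth that the Sample size section assumes, rates from birth and from enrolment are on the same scale, and power is unchanged if the SD of the rate is the same. The exact model response would normally be set in the analysis plan, which is not shown. Parents may also be approached before birth, so some infants could be enrolled early, with little mismatch.

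Much of this stands, and it rules out three stronger readings that a reader might infer.

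- **Three incompatible primary outcomes.** The documents do not support this. Primary analysis refers back to the primary outcome in the same sentence, so its mention of change is loose wording rather than a rival definition.
- **Varying intervals make raw change unreliable.** A six-day spread moves one infant's change by 6 × 24/28 = 5.1 mm, but the effect on the group SD is about 0.05 to 0.16 mm. The documents give no reason for intervals to differ by arm.
- **True power is 57% to 71%.** This needs the SD of the change to stay at 12 mm over a shorter window. If that were because all the variation is measurement error, each reading would carry an error SD of 12/√2 = 8.5 mm, over a third of the 24 mm mean growth. Nothing in the documents supports that. Nor does the protocol say when the first measurement was taken in the historical data.

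The objection does not remove the conflict over the start point. Linearity puts the two rates on the same scale, but it does not make them equal when the treatment changes at randomisation. The Sample size section, moreover, names the first 28 days after birth as the outcome being powered.

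**Conclusion.** The concern holds as a contradiction about the start point of the primary outcome: enrolment in the Primary objective and Study schedule, against the first 28 days of life or after birth in the abstract, Hypothesis and Sample size sections.

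If birth is used, a 6 mm/28 d effect that begins at day 3 to 5 shrinks to about 5.4 to 4.9 mm, with power of about 68% to 61%. This assumes SD 12 mm, 60 per group, and that the 6 mm is the velocity difference while on study nutrition; the protocol does not say whether it already allows for the shared scNPN period.

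If enrolment is used, power is 77.5% at best among the cases examined, when the rate SD stays at 12 mm/28 d. That shortfall from 80% comes from the plan's own inputs, not from the window. Lower values are possible under the SD assumptions shown, but they are sensitivity figures only.

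**What to change.** 1. Make the Primary objective quantity the single primary outcome: head circumference at day 27-29 minus that at enrolment, divided by exact elapsed time and expressed in mm/28 days.
2. Use that outcome in the abstract, Hypothesis and Primary analysis sections, and for the outcome named in the Sample size section.
3. Leave unchanged the sentence in Sample size that reports the historical first-28-day data. Add that its SD of 12 mm/28 d is assumed to carry over to the enrolment-to-day-27-29 window.
4. Restate the power as 77.5% with 60 survivors per group under that assumption. Give as sensitivity, for assumed 22-26 day windows, 67.3% to 74.5% (SD of the change scaling with √time) and 56.9% to 71.3% (SD of the change fixed at 12 mm).

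The cost is wording in four sections and one short calculation. No new data are needed, and the change should be made before the primary analysis.

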### Secondary analysis to facilitate interpretation of the primary outcome

a) Developing a non-linear model of early head growth (if data analysis indicates this is required)

b) Longitudinal joint modelling of head growth and survival;

c) Longitudinal joint modelling of head growth and protein/calorie intake

d) per protocol analysis omitting babies that received PN other than that due under their allocation for more than 24 hours;

e) exploratory data analysis of how potential confounding variables are distributed between the two intervention groups

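### The stated primary model names neither the gestation stratum nor enrolment head circumference as a covariate: the test is valid, but precision that costs nothing is left unclaimed

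*Protocol article*

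**What the plan says.** The Primary analysis section fixes the population and the model. On the population: "Primary analysis of the data will be by intention to treat, and will be done for all survivors". On the model: "while taking account of the clustering arising from multiple pregnancies, the primary outcome will be assessed using a general linear model". Multiple-birth clustering is the only feature that the model is said to account for. No covariate is named, and neither is the device that will carry the clustering.

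Four other places bear on this:

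- Randomisation: "The randomisation list will be stratified by gestation at birth: 24-26 and 27-28 completed weeks gestation at birth". The same section adds: "In the case of multiple births, each infant will be individually randomised".
- Study schedule: after randomisation, "baseline growth measurements will be performed", so an enrolment head circumference exists for each infant.
- Primary objective: the outcome is "the rate of head growth from measurement made at enrolment to a measurement made between 27 and 29 completed days after birth", a change divided by elapsed time. Baseline therefore enters by subtraction.
- Analysis: a separate data analysis plan is to be completed once two thirds of infants are recruited. The reason given for that timing is experience with missing data.

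**The concern.** When randomisation is stratified on a factor that predicts the outcome, the arms are balanced on that factor and the treatment difference varies less between hypothetical repetitions of the trial. A model without the stratum still counts the between-stratum variation as residual error. Its standard error is then larger than the true sampling variation, and the test is slightly conservative.

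Enrolment head circumference was not a stratification factor. The unadjusted standard error is correct for the unadjusted estimate there, but larger than it need be. Subtracting baseline is not the same as adjusting for it. Subtraction fixes the baseline coefficient in advance, whereas a covariate lets the data estimate it, which is generally at least as precise.

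Precision is what is at stake. The planned number analysed gives slightly less than the stated 80% power, so a gain that needs no extra infants is worth having.

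**Working it through.** **Inputs from the protocol (Sample size section):** difference 6 mm over 28 days (24 against 30), SD 12 mm, two-sided 0.05, two-group t-test, 75 recruited per group, 80% survival. Analysed per group: 75 × 0.8 = 60.

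**Inputs not in the protocol, so assumed:** share of outcome variance explained by stratum and enrolment head circumference together (R²) 0.05 to 0.30; difference between strata 0 or 6 mm; 20% or 30% of infants in twin pairs; within-pregnancy correlation 0, 0.3 or 0.6.

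**Step 1. The plan's own figure.** SE = 12 × √(2/60) = 2.19 mm, and 6/2.19 = 2.74. Normal approximation: power = Φ(2.74 − 1.96) = 78.2%. Exact t-test: 77.5%. Both are a little below the stated 80%. This shortfall is a separate matter and serves here only as the starting point.

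**Step 2. Adding covariates.** The residual SD becomes 12 × √(1 − R²), and the SE shrinks by the same factor.

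| Assumed R² | Residual SD (mm) | SE (mm) | 6/SE | Power, normal | Power, t-test |
|---|---|---|---|---|---|
| 0 | 12.00 | 2.19 | 2.74 | 78.2% | 77.5% |
| 0.05 | 11.70 | 2.14 | 2.81 | 80.2% | 79.6% |
| 0.10 | 11.38 | 2.08 | 2.89 | 82.3% | 81.7% |
| 0.20 | 10.73 | 1.96 | 3.06 | 86.5% | 85.9% |
| 0.30 | 10.04 | 1.83 | 3.27 | 90.5% | 90.1% |

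On the t-test scale the gains are 2.1, 4.2, 8.4 and 12.6 points. At R² = 0.05 the normal-approximation requirement falls from 63 to 60 analysed per group, and 60/0.8 = 75 is the number planned.

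**Step 3. The stratum alone.** With equal strata 6 mm apart, the between-stratum variance is (6/2)² = 9, and 9/144 = 6.25% of the total. This was simulated with 120 analysed infants, each randomised individually in blocks of 4 (assumed) within stratum, with total SD 12 mm. Across the six combinations of twin share and correlation, adding the stratum raised power by 1.7 to 2.3 points (for example 77.4% to 79.25%, and 78.55% to 80.83%).

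**Step 4. Validity.** These are type I error rates from the same simulation, at nominal 0.05.

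- No stratum, clustering ignored, strata equal: 0.0407 to 0.0530.
- No stratum, clustering ignored, strata 6 mm apart: 0.0378 to 0.0468.
- Stratum included, clustering ignored, strata 6 mm apart: 0.0445 to 0.0525.
- Stratum included, cluster-robust standard errors, all settings: 0.0448 to 0.0563.

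Leaving out the stratum does not inflate the error rate. It lowers it a little when strata differ.

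**Step 5. A caution on the clustering device.** A crude two-step generalised least squares fit, with the sibling correlation estimated from only 12 or 18 pairs, had type I error of 0.0523 to 0.0877, highest at correlation 0.6. This is not the same as a properly fitted mixed model. It does show that with few pairs the estimation method and degrees of freedom need care.

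**The case against.** The strongest reply is that silence is not exclusion. The section gives no covariate list of any kind, an article condenses, and a data analysis plan is promised where covariates are normally fixed. Baseline is already in the outcome by subtraction. The size of any gain rests on R² values that the protocol does not supply.

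Much of this stands. Nothing says that the stratum will be left out, the R² values are assumptions, and an unadjusted comparison is legitimate. What remains is that the section does state the primary model and the one design feature it accounts for. The stratification factor is another design feature and is not there. The reason given for the later plan is missing data rather than the choice of model.

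A reader might infer more than the text supports:

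- *That a general linear model cannot handle siblings.* A linear model can carry a family random effect, correlated errors or cluster-robust standard errors, and the sentence says that clustering will be taken into account. Not naming the device is missing detail, not an error.
- *That family would be entered as a fixed effect, discarding singletons.* The protocol nowhere proposes this.
- *That item (e) under Secondary analysis to facilitate interpretation of the primary outcome opens the way to adjustment after imbalance is seen.* It promises only "exploratory data analysis of how potential confounding variables are distributed between the two intervention groups", as a secondary and descriptive look, and mentions no adjustment.
- *That the primary test is invalid.* Siblings are randomised individually, and Step 4 shows no inflation of the unadjusted test even when clustering is ignored.

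**Conclusion.** The point holds as a modest, cost-free improvement in precision. The test as stated is valid and at worst slightly conservative. At 60 analysed per group, power rises from 77.5% to about 80%, 82% or 86% if stratum and enrolment head circumference explain 5%, 10% or 20% of the variance. The stratum alone is worth about 2 points at a 6 mm difference between strata. If neither variable predicts head growth, there is practically nothing to gain and nothing to lose. No gain from modelling siblings is counted, because the protocol already says that clustering will be accounted for.

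**What to change.** State the primary model in the Primary analysis section, or in the data analysis plan before any comparison by arm, along these lines: a linear model for head growth velocity with fixed effects for arm, gestation stratum (24-26 or 27-28 weeks) and enrolment head circumference, with clustering on mother handled by a random intercept. GEE or cluster-robust standard errors on mother are acceptable alternatives.

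Two details belong in the same sentence. First, if a random intercept is used, specify restricted maximum likelihood with small-sample degrees of freedom, given how few sibling pairs there may be. Second, specify that the enrolment measurement used as covariate is the one taken before study PN starts, as the order of the Study schedule section suggests.

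The cost is one or two sentences. The variables are already collected, and neither the sample size nor the conduct of the trial changes.
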